## Abstract

**Background::**

Depression is a common mental illness often associated with insomnia. Baduanjin exercise has been found to improve depressive symptoms and has also been found to have good effects on insomnia. However, there are no rigorous clinical studies to evaluate the effects of Baduanjin exercise on depressed patients with insomnia, so this randomized controlled trial will evaluate the efficacy of Qigong Baduanjin exercise in treating depression with insomnia.

**Methods::**

This is a prospective randomized controlled trial to investigate the clinical efficacy of Baduanjin exercise in the treatment of depression with insomnia. The included patients will be randomly divided into a treatment group and control group. The treatment group will be treated with Baduanjin exercise and the control group will be treated with oral mirtazapine. After 8 weeks of continuous treatment, they will be followed up for 3 months. Observed indexes included Pittsburgh sleep quality index, Hamilton expression Rating Scale score, and adverse reactions. Finally, the data are statistically analyzed by SPSS 20.0 software.

**Discussion::**

This study will evaluate the efficacy and safety of Baduanjin exercise in the treatment of depression with insomnia, and the results of this study will provide a clinical basis for the treatment of depression with insomnia.

**Trial registration:** OSF Registration number: DOI 10.17605/OSF.IO/KC48H

## Introduction

1

Major depressive disorder is a chronic psychiatric disorder characterized by significant and persistent depression. It is one of the most common mental disorders.^[1]^ Clinical manifestations include persistent depressed mood, slowed thinking, and reduced energy, while some patients may experience loss of appetite, low self-esteem and, in some cases, suicidal tendencies.^[2–4]^ Some studies have shown that the prevalence of major depression in China is 3.02%,^[5]^ while the prevalence of depression in China reaches 7.3% in 2020 as people's life stresses increase with the development of the times,^[6]^ while among adolescents, 24.6% are detected to have depression.^[7]^ Most patients with depression are accompanied by sleep disorders, with 1 survey showing that 90% of patients diagnosed with depression have sleep disorders.^[8]^ On the other hand, insomnia is a potential risk factor for depression, which can aggravate the condition and lead to prolonged depression, thus seriously affecting the patient's life and work, so effective treatment can better alleviate the patient's condition and reduce the huge financial burden on the family and society.

At present, anti-insomnia drugs are often used to treat depression with insomnia, but long-term oral western medicine will produce drug resistance, and the increasing drug dose and adverse reactions of drugs will affect the health of patients. Baduanjin exercise is a traditional Chinese Qigong sport, which emphasizes the integration of body and mind. As a low-energy exercise, Baduanjin exercise can not only enhance the physique, but also regulate people's mood, so that people can reduce pressure and relax in the process of exercising. It has the effect of prevention and adjuvant treatment of physical and mental diseases.^[9,10]^ Although it has been suggested that Baduanjin exercise can improve depression and sleep quality in patients,^[11]^ there are no rigorous randomized controlled studies to evaluate the clinical efficacy of Baduanjin exercise in the treatment of depression combined with insomnia, and there is a lack of long-term follow-up observations. Therefore, this study intends to evaluate the efficacy and safety of Baduanjin exercise in the treatment of depression with insomnia through a prospective randomized controlled trial.

## Materials and methods

2

### Study design

2.1

This is a prospective randomized controlled study to study the efficacy and safety of Baduanjin exercise in the treatment of depression with insomnia. The patients will be randomly divided into a treatment group and control group. The treatment group will take Baduanjin exercise, and the control group will take mirtazapine tablets orally. After 8 weeks of continuous treatment, they will be followed up for 3 months. The flow diagram is shown in Fig. 1. This research scheme follows the latest Consolidated Standards of reporting trials (2017) and standard protocol items: recommendations for interactive trials 2013 statement.

**Figure 1 F1:**
[figure not shown]
Flow diagram.

### Ethics and registration

2.2

This research protocol complies with the declaration of Helsinki and ethical guidelines for clinical research, and has been registered in the open science framework (Registration Number: DOI 10.17605/OSF.IO/KC48H) with the approval of the Committee of clinical research ethics of our hospital. Before the start of the study, we will inform patients of the methods and potential risks of the study. After obtaining their written informed consent, they will be randomly divided into groups. During the study, they can freely choose whether to continue the trial at any time.

### Patients

2.3

#### Basis of diagnosis

2.3.1

Refer to the Chinese Classification and Diagnostic Criteria for Mental Disorders, 3rd Edition (CCMD-3)^[12]^ for the diagnostic criteria of depression and insomnia.

#### Inclusion criteria

2.3.2

(1)Meet the diagnostic criteria for depression and insomnia.(2)Those with a Hamilton Depression Rating Scale score ≥24.(3)Age ≥18 and ≤60 years.(4)Not taking antidepressant or sleep-aid medication (including traditional Chinese medicine and western medicines) within the last 2 weeks.(5)Patient signed an informed consent form.

#### Exclusion criteria

2.3.3

(1)Patients with a psychiatric disorder other than depression.(2)Patients with insomnia due to other diseases or medications.(3)Patients with alcoholism, psychoactive substances, drug abusers, and those who are dependent.(4)Women who are pregnant, preparing for pregnancy, or breastfeeding.(5)Those who have participated or are participating in other clinical trials within the last 1 month.

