### Sample size

2.4

Sample size estimates are based on the mean and standard deviation of the Pittsburgh sleep quality index^[13]^ scores of patients after 8 weeks of treatment, referencing the pre-test results of 11.24 ± 5.03 for the treatment group and 14.27 ± 5.31 for the control group, set at α = 0.025, one-sided test, β = 0.20. Calculated by PASS 15.0 software to require 47 participants per group. With an estimated drop-out rate of 10%, 53 patients will be included in each group.

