### Recruitment strategy and distribution plan

2.5

Participants will be screened among patients attending outpatient clinics and recruitment information will be disseminated through the distribution of brochures and posted on the Internet and WeChat platforms to widen the scope of screening. Participants who meet the inclusion criteria will be fully informed of the purpose and protocol of the study and informed consent signed by the participants will be obtained.

The study will randomly assign patients who meet the criteria for either the treatment group (Baduanjin exercise group) or the control group (Western medicine group) in a 1:1 ratio through a central network-based randomization tool. The random numbers are generated by a statistician using a computer software program and these random numbers are placed in sealed opaque envelopes which are handed to the participants by the study coordinator. Due to the specific nature of the intervention, the patient and the operating physician are knowledgeable about the assigned outcome. However, the assessors of the study results and the statisticians who counted and analyzed the data are unaware of the allocation.

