### Interventions

2.6

Patients in both groups will be given health guidance and psychological counseling and maintained their current lifestyle. The treatment group will receive regular Baduanjin exercise. The Baduanjin exercise used in this study is the Baduanjin exercise of Fitness Qigong developed by the General Administration of Sports of China, which consists of 8 main movements. A medical practitioner who has been practicing Baduanjin exercise for 10 years will explain the key points of Baduanjin exercise and give step-by-step instructions to ensure that each patient learns it completely and is issued with a DVD tutorial. Patients will practice at home once a day, 5 times a week, for 30 minutes each time for a total of 8 weeks. The control group will be given oral mirtazapine tablets (N.V. Organon, Netherlands, H20090160) at 15 mg once a day at bedtime, 5 times a week for 8 weeks.

Patients will record in the case report form details of the time taken or practiced, and any discomfort that occurs during the study.

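### The five printed exclusion criteria do not exclude current suicide risk, although entry requires a Hamilton score of 24 or more and no recent antidepressant

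*Protocol article*

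**What the plan says.** Section 2.3.2 (Inclusion criteria) sets a floor on severity and a medication-free period. Criterion (2) is "Those with a Hamilton Depression Rating Scale score ≥24". Criterion (4) begins "Not taking antidepressant or sleep-aid medication" and covers the last 2 weeks.

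Section 2.3.3 (Exclusion criteria) is a numbered list of five. The first is "Patients with a psychiatric disorder other than depression". The other four concern secondary insomnia, substance misuse or dependence, pregnancy and breastfeeding, and recent or current participation in another trial.

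Section 2.5 acts directly on these lists: "The study will randomly assign patients who meet the criteria", with 1:1 allocation. Under 2.6 the treatment arm learns the exercise and then "Patients will practice at home once a day, 5 times a week", for 8 weeks. Only the control arm receives mirtazapine. Both arms receive general health advice and psychological counseling.

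The Introduction lists, among the features of depression in some patients, "low self-esteem and, in some cases, suicidal tendencies".

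**The concern.** The entry rule selects patients with a substantial depression score who are not on an antidepressant, and one arm keeps them off antidepressants for 8 weeks while they practise at home. The article itself names suicidality as a feature of this disorder in some patients, yet nothing in the printed eligibility rules acts on it. A site that follows the lists to the letter would have no printed ground for turning away a patient with current suicide risk who met everything else.

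What is at stake is patient safety at the point of entry. No estimate, test or sample-size figure is affected.

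**Working it through.** This is a check of text against text, with one line of arithmetic for the number of patients the rule governs.

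**Step 1. Does any exclusion in 2.3.3 cover suicide risk?**

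| Exclusion | Subject | Covers current suicide risk? |
|---|---|---|
| (1) | Psychiatric disorder, with depression exempted | No: suicidality arising from the depression falls within the exemption |
| (2) | Insomnia with another cause | No |
| (3) | Alcohol or drug misuse, dependence | No |
| (4) | Pregnancy, planned pregnancy, breastfeeding | No |
| (5) | Another trial within 1 month | No |

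Result: 0 of 5.

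**Step 2. Does any inclusion criterion in 2.3.2 cover it indirectly?** The five are diagnosis, a Hamilton score of at least 24, age 18 to 60, no antidepressant or sleep aid in the last 2 weeks, and signed consent. Result: 0 of 5. None of the printed inclusion or exclusion criteria leaves room for investigator judgment; that phrase appears only in 2.3.4, for discontinuation.

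**Step 3. Do the other stated safeguards bar entry?**

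| Safeguard | Section | What it does | Bars entry? |
|---|---|---|---|
| Ethics approval | 2.2 | Approves the research protocol | No |
| Disclosure and written consent ("we will inform patients of the methods and potential risks of the study") | 2.2 | Informs the patient | No |
| Freedom to leave at any time | 2.2 | Acts during the study, on the patient's initiative | No |
| Discontinuation for serious events or complications, with emergency treatment | 2.3.4(1) | Acts once such an event has occurred | No |
| Health advice and counseling, both arms | 2.6 | Part of the treatment package; not described as screening | No |
| Patient record of discomfort | 2.6 | Acts during treatment | No |
| Periodic progress review by an independent research assistant | 2.8 | Acts during the study | No |

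**Step 4. What follows from applying the rule?** Take a patient who has the diagnoses, a Hamilton score of 24 or more, no medication for 2 weeks, and current suicide risk. Such a patient meets 2.3.2, is not caught by 2.3.3, and is therefore randomized under 2.5 to either arm.

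**Step 5. How many patients does the rule govern?** Section 2.4 states "53 patients will be included in each group". With two arms, 2 × 53 = 106. This is the number whose entry the list decides, not the number at risk. The document gives no proportion with suicide risk, so the latter cannot be computed.

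**The case against.** The strongest objection is that this is an omission from a condensed journal article. Section 2.2 reports ethics approval of a research protocol that may be fuller than the article, and that protocol may exclude suicide risk. Nothing in 2.3.3 is false, and no other section contradicts it. In part this stands: that the printed list is complete is an inference, and the point depends on it. But eligibility lists are normally printed in full in a protocol article. This one is numbered, goes down to planned pregnancy and trials within 1 month, and refers to no further criteria. It is fair to review it as the stated entry rule.

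Second, the exercise arm is not left without care. That is right: counseling is given in both arms, consent is informed, and 2.3.4(1) allows discontinuation with emergency treatment. These reduce the consequence of the gap but do not close it, since none acts as an entry criterion.

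Third, the Introduction describes depression in general and does not say that suicidal patients will be enrolled. That also stands. It shows that the hazard was known when the criteria were written; it does not make the document inconsistent.

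Fourth, a minimum Hamilton score without an upper limit is not itself an error, and the document links no Hamilton total to suicide risk. Agreed; the score is context here, not evidence of how many patients are at risk.

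**Conclusion.** The point holds in a limited form: the printed criteria do not exclude current suicide risk, so such a patient can enter either arm, including the one without an antidepressant. It should be corrected. Confidence is moderate, because the conclusion assumes that the printed list is the whole list.

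Three stronger readings are tempting and are not supported.

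- A reader might infer that 1:1 allocation exposes half of the at-risk patients to harm by denying them mirtazapine. The one-in-two chance is simply the allocation ratio and applies to every patient. No section says that mirtazapine at 15 mg, given 5 times a week, protects a patient at suicide risk. The gap concerns both arms equally.
- A reader might infer that safety monitoring or stopping rules are missing. The article states several provisions (Step 3), and further detail may properly sit in the full protocol.
- A reader might infer that an appreciable share of the 106 patients would be at risk. No such share can be derived from the document.

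**What to change.** Add one line to 2.3.3:

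*(6) Patients with current suicide risk, as judged by the investigator at the baseline assessment, who are referred for care.*

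Investigator judgment is enough. The criterion should not be tied to a particular Hamilton item, since 2.7 gives only the number of items and names none. If the full protocol already has such an exclusion, the published list should be corrected to show it.

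The cost is small. It needs one protocol amendment, for which 2.8 already provides ethics re-approval. No visit is added, because inclusion criterion (2) already requires a clinical rating before entry. Recruitment will be slightly slower, and the results will apply only to patients without current suicide risk, which the report should state. The planned 53 per arm can stay as it is.

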#### Discontinuation criteria and treatment

2.3.4

(1)Those who experience serious adverse events or other complications, etc, and who, in the judgment of the investigator, should be discontinued from the trial and given appropriate life-saving treatment.(2)Subjects who have poor compliance and are unable to complete the entire set of Baduanjin exercise movements, which have an impact on the study results.(3)Subjects who, for whatever reason, are unwilling or unable to continue with the clinical trial and request the investigator to withdraw from the trial and discontinue the trial.

For discontinued cases or lost cases, the investigator should complete the last test possible for analysis of their efficacy and safety. For all discontinued cases, the reason for the discontinuation should be entered on the case report form.

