### Outcomes

2.7

(1)Pittsburgh sleep quality index^[13]^: including sleep quality, time to sleep, sleep duration, sleep efficiency, hypnotic medication, sleep disturbance, and daytime functioning. After scoring respectively, the total score is 21. The higher the score, the worse the sleep quality.(2)Hamilton Depression Rating Scale^[14]^: it includes 24 items. The higher the score, the heavier the symptoms.(3)Incidence of adverse reactions: including treatment-related discomfort experienced by patients during the study period.

Two research assistants who are unclear about the outcome of the subgroups will score the 2 groups of patients according to outcome indicators before treatment, at the end of treatment, and at month 1 and month 3 of the end of treatment, through outpatient visits.

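### Discontinuation for failing to complete the Baduanjin set can, on its natural reading, occur only in the exercise arm, and the scheduled assessments are not secured for patients discontinued this way

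*Protocol article*

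**What the plan says.** All references are to the protocol article.

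- **Criterion (2), section 2.3.4:** "Subjects who have poor compliance and are unable to complete the entire set of Baduanjin exercise movements", with the added qualifier that this affects the results.
- **Who does what, section 2.1:** "The treatment group will take Baduanjin exercise, and the control group will take mirtazapine tablets orally". Section 2.6 agrees, and has patients in both groups record practice or tablet intake.
- **Scope, section 2.3.4:** criterion (1) speaks of patients who "should be discontinued from the trial and given appropriate life-saving treatment". Criterion (3) also concerns leaving the trial. Criterion (2) does not state its scope.
- **After discontinuation, section 2.3.4:** "For discontinued cases or lost cases, the investigator should complete the last test possible for analysis of their efficacy and safety".
- **Schedule, section 2.7:** two assistants unaware of allocation score patients "before treatment, at the end of treatment, and at month 1 and month 3 of the end of treatment".
- **Blinding, section 2.5:** patient and treating physician know the allocation; outcome assessors and statisticians do not.

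**The concern.** Randomisation makes the groups comparable only while patients are kept and measured in the same way in both. Criterion (2) depends on something that happens after allocation and that only one group is asked to do. Patients who comply poorly and cannot manage the movements may well differ in prognosis from those who can. That is plausible in a population entering with a Hamilton score of at least 24, though the article offers no data on it.

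If such patients leave the exercise arm and their counterparts stay in the mirtazapine arm, the exercise results drift towards patients able and willing to exercise, while the control results are not filtered in that way. The later visits are the most exposed, because the text on discontinued cases makes no provision for them. An analysis plan can choose how to handle missing scores, but it cannot restore scores that were never collected. That makes this a matter for the protocol.

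**Working it through.** **1. The plan's own figure.** Inputs from section 2.4: PSQI after 8 weeks 11.24 ± 5.03 (exercise) and 14.27 ± 5.31 (control), one-sided α = 0.025, β = 0.20, drop-out 10%.

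- Difference: 14.27 − 11.24 = 3.03.
- Common SD: √((5.03² + 5.31²)/2) = 5.172.
- Normal approximation: n = 2(1.960 + 0.842)² × 5.172² / 3.03² = 45.7, so 46. With the noncentral t distribution, power is 0.794 at 46 and 0.802 at 47, so 47 per group.
- Drop-out: 47/0.90 = 52.2, so 53.

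The stated 47 and 53 reproduce. The point does not depend on them, and the fix leaves them unchanged.

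**2. The sections side by side.**

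- *Can a control patient meet criterion (2)?* It asks for poor compliance together with inability to complete the Baduanjin set. Sections 2.1 and 2.6 give Baduanjin to the treatment group only. On the natural reading, no.
- *Is there a counterpart for mirtazapine?* None is listed, although section 2.6 collects intake records that could support one. Criterion (3), the patient's own wish or inability to continue, applies to both arms.
- *What is measured afterwards?* Section 2.3.4 provides a last possible test. Section 2.7 has no visit between baseline and the end of treatment. A test taken when a patient stops before week 8 is therefore not a week-8 value; for a patient stopped close to week 8 it could be. Section 2.3.4 does not mention the month-1 and month-3 visits.

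**3. Size if removed patients are left out of a visit's comparison (illustration).** The article gives neither a removal rate nor a compliance-outcome correlation, so both are assumed. Suppose a fraction p of the exercise arm is removed from the worst tail of a variable that correlates ρ with PSQI. The mean of those remaining then falls by

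shift = SD × ρ × φ(z₁₋ₚ)/(1 − p), with SD = 5.03.

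- p = 0.10: φ(1.282)/0.90 = 0.195, so the shift is 0.29 for ρ = 0.3 and 0.49 for ρ = 0.5. The upper bound, ρ = 1.0, is 0.98.
- p = 0.20: φ(0.842)/0.80 = 0.350, so the shift is 0.53 for ρ = 0.3 and 0.88 for ρ = 0.5. The upper bound is 1.76.

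At 10% removal and ρ of 0.3 to 0.5, the shift is 0.29/3.03 = 10% to 0.49/3.03 = 16% of the planned difference.

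In simpler terms, shift = p × g, where g is how much worse the removed patients fare than those who remain. At p = 0.10, shifts of 0.29 and 0.49 correspond to g of 2.9 and 4.9 PSQI points.

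**4. Effect on the error rate.** With no true difference and 47 against 53 patients analysed, SE = 5.172 × √(1/47 + 1/53) = 1.036. A shift of 0.3 raises the one-sided error from 0.025 to 1 − Φ(1.960 − 0.3/1.036) = 0.047. A shift of 0.5 raises it to 0.070.

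**5. If the early score is used as the week-8 value.** A patient tested early may not yet have improved, which counts against exercise. Or the patient may later have worsened without its being recorded, which favours exercise. The direction cannot be derived from the document.

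**The case against.** The wording can be read more gently. The criterion joins poor compliance with inability to complete the set, and adds that this must affect the results, so a patient who merely skips sessions does not clearly meet it. The conjunction might even be meant to join two groups, in which case poor compliance could cover tablets as well. Criterion (2) does not itself say that the patient leaves the trial, and the article does not name who applies it. The phrase "the investigator should complete the last test possible for analysis of their efficacy and safety" does not say that this is the only test or that later visits are cancelled. Outcome assessors and statisticians are blinded.

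Much of this stands as a limit on how far the point can go. A reader might infer that removed patients certainly have no follow-up data, or that the scores of the two arms are simply not comparable. The document does not establish either: the off-schedule test and the absent follow-up are inferred from what section 2.3.4 provides and leaves unsaid. A reader might also fault the tests in section 2.9 for lacking an analysis set or a missing-data method, but those may sit in an analysis plan that is not shown.

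The illustration also has limits. It treats the 10% drop-out, an all-cause rate, as if it all arose under criterion (2). It assumes removal of a clean tail and no offsetting losses in the control arm.

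What the objection does not remove is that the only listed compliance criterion names the exercise, that both neighbouring criteria concern leaving the trial, and that nothing in the section secures the scheduled visits. Blinded scoring does not protect against selective loss of the patients to be scored.

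**Conclusion.** The point holds as a risk written into section 2.3.4. Followed on its natural reading, criterion (2) produces loss after randomisation in one arm only, and the section does not secure week-8, month-1 or month-3 scores for those affected.

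If they are left out, the bias favours exercise: about 0.3 to 0.5 PSQI points at an assumed 10% removal and correlation of 0.3 to 0.5, against a planned 3.03. The true size depends on how many patients are removed and how they fare, and the article gives neither. If the early score is used as the week-8 value, the direction is uncertain. The text should be corrected before enrolment, because visits not made cannot be recovered.

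**What to change.** - Reword criterion (2) so that poor compliance, or inability to complete the movements, is not a reason to leave the trial's assessments. Whether the patient continues the intervention remains a clinical decision.
- State that every randomised patient who has not withdrawn consent is assessed at week 8, month 1 and month 3 by the blinded assessors, and is counted in the assigned group.
- State that a test taken early on discontinuation is not used as the week-8 score.
- Report compliance in both arms from the practice and intake records already kept under section 2.6.

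The cost is protocol wording and the effort of keeping non-compliant patients on visits that are already planned; 47 and 53 per group stand. The downside is that the estimate includes poor compliers and may be smaller. A check before randomisation that candidates can perform the movements is not advised, since it adds a procedure and risks teaching the intervention to future controls. How remaining missing scores are modelled can be left to the analysis plan.
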